### Intervention

Both groups receive a set of 12 Mood Memos emails over 6 weeks. The Mood Memos emails are written in html to look as engaging as possible. Emails are also written in plain-text for participants who cannot or who choose not to receive html emails. Email design and layout was tested in all of the major email clients, using the services of Litmus [21] and Email on Acid [22]. Each email includes identification of the recipient and how they got on the mailing list, and provides the opportunity to withdraw from the study by choosing not to receive further Mood Memos emails and/or complete further assessment.

### Active group

Email messages for the intervention group are based on self-help strategies endorsed by depression experts [10] (see Table 1 for an overview). These self-help strategies were expanded into lengthier email messages. The emails aim to change participant behaviour rather than passively increase knowledge, and as such, their design was informed by theories of behaviour change, persuasion, health communication, and communication on the web [23-32]. Each message contains a brief overview of the strategy, a lengthier explanation of the strategy, why the strategy would work, tips on how the strategy could be implemented, suggested solutions for barriers to implementing the strategy, and an appeal to commit to implementing the strategy. The content of the messages (e.g., strategy rationales, potential barriers and solutions) was derived from professional books, and posts on depression forums by consumers [33-37]. Messages were refined further by a working group of mental health researchers (including consumer researchers). The messages have minimal tailoring to individual participant characteristics [38]. For example, links to internet resources are tailored based on country of residence and the wording advocating each strategy is tailored to the participant's familiarity with using each strategy [29], as indicated during the baseline questionnaire. The strategies are ordered from highest to lowest feasibility to carry out, based on rankings from the original expert study [10]. This is consistent with clinical advice [39,40] to start homework with simple, feasible tasks and build up with time and success.

**Table 1 T1:** Overview of Mood Memos Emails

Order	Active	Control
**1**	Get out of the house	What is depression?

**2**	Fight the desire to do nothing	What types of depression are there?

**3**	Set yourself a small goal and reward yourself for reaching it	Can depression cause physical health problems?

**4**	Eat well	Depression and other mental health problems

**5**	Improve your sleep habits	What is the history of depression?

**6**	Do something you enjoy and that gives you a sense of achievement	What causes depression?

**7**	Talk to someone supportive about your problems and how you feel	Who is at risk of depression?

**8**	Get active	How common is depression?

**9**	Do what has worked for you in the past	Burden of depression

**10**	Let others know how you are feeling	Is depression a weakness?

**11**	Ask someone you trust to help you get out and do things	Does depression re-occur?

**12**	Learn relaxation techniques	Depression across cultures

### Control group

The control group will receive email messages containing general information about depressive disorders (see Table 1 for an overview). The messages are designed to be interesting but of no therapeutic value. Their role is to control for the effect of receiving emails with depression-related content. The order of the messages was chosen to follow a reasonably logical progression from basic or essential information to more advanced or less essential information. The messages are not tailored, and critically, they do not include suggestions for action or setting goals. Message content was sourced from recently published psychiatry textbooks, and supplemented with recent reviews or meta-analyses as required.

### Assessment

Assessment is conducted at baseline (immediately prior to receiving the first Mood Memos email), midway through the intervention (3 weeks post-baseline), at the end of the intervention (6 weeks post-baseline), and 6 months after the end of the intervention (see Table 2 for outcome measures and time points of assessment). All assessment is based on self-report and is completed on the project website. The assessment is aimed to take little time to complete in order to discourage dropout attrition [41] whilst providing critical data. Time to complete questionnaires is estimated to range from 2 minutes (mid-intervention and 6-month follow-up assessment) to 6 minutes (for baseline and post-intervention assessment). The primary outcome is depression symptom severity (assessed with the PHQ-9 [42]). This outcome will also be categorised to yield probable depression diagnoses. Secondary outcomes are psychological distress (assessed with the K10 [43]) and level of functioning (assessed with the Work and Social Adjustment Scale [44]).

**Table 2 T2:** Outcome measures and timepoints of assessment

Assessment	Screening	Baseline	Mid-intervention	Post-intervention	6 months follow up
List of Threatening Experiences		X			

Sociodemographics		X			

PHQ-9	X		X	X	X

K10		X	X	X	X

Work and Social Adjustment Scale		X	X	X	X

Self-efficacy		X		X	

Knowledge of depression		X		X	

Coping questionnaire		X		X	

Help-seeking question			X	X	X

Qualitative feedback				X	

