### Trial procedure

The administration of the intervention is fully automated using PHP 5 and a MySQL 5 database. Participants who visit the project website and give their informed consent to participate are screened for sub-threshold depression. They will be categorised into one of three depression status groups based on their results:

1) Sub-threshold depression: 2 to 4 symptoms of depression present for more than half the days or nearly every day (except for suicidality, which is counted as a symptom if present for only several days or more), for 2 weeks or more, with significant impact on functioning

2) Probable major depression: 5 or more symptoms of depression present for more than half the days or nearly every day (except for suicidality, which is counted as a symptom if present for only several days or more), for 2 weeks or more, with significant impact on functioning

3) Non-depressed: not meeting criteria for sub-threshold or major depression, i.e. too few symptoms, too short duration, little or no impact on functioning.

Depression symptoms are defined as the nine symptoms in criterion A of DSM-IV Major Depressive Episode [16] assessed with the PHQ-9 (see Assessment below). Depression status is scored by the system and trial eligibility is determined immediately, based on admission criteria. Those whose results indicate major depression or non-depressed will be given feedback on their score and informed that they are not eligible to participate. In addition, those with major depression will be encouraged to seek professional help and will be directed to a section on the website that provides contact details of organisations that provide help or support for mental disorders, broken down by country.

Participants with a positive screen for sub-threshold depression will be assessed to see whether they meet further inclusion criteria (see admission criteria above) and asked to provide their name or a pseudonym and an email address. An email will be sent to the address provided, which will contain a link to the baseline questionnaire package. Once the baseline assessment is completed, participants will be randomised to the active group or control group using the mt_rand() PHP script. Immediately following randomisation, participants will be sent their first Mood Memos email.

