### Statistical analysis

Primary effectiveness analyses will be undertaken on an intention-to-treat basis. Any participants who were randomised but who withdraw from the study, or who take up alternative treatments, will be included in the analysis as randomised. Continuous outcomes (PHQ-9 scores, K10 scores, WSAS scores) will be evaluated using mixed models for repeated measures (MMRM) [68]. This method of analysis will be utilised because of its ability to include participants with missing data under the assumption that observations are missing at random (MAR). The inclusion of an additional measurement occasion halfway through the intervention should increase the tenability of the MAR assumption. *A priori *contrasts will compare change from baseline at the primary endpoint (post-intervention) and at 6-months follow up. Dichotomous outcomes will be defined. These include the development of probable major depression (as indicated by PHQ-9 results) in participants who did not meet this criterion at baseline and remission from sub-threshold depression in those who fell into this category at baseline. Relative risk will be calculated and tested for significance. The numbers needed to treat to avoid one person developing major depression and to achieve one remission from sub-threshold depression will be calculated.

In addition to intervention group, a number of variables will be examined to see if they predict outcomes: age, gender, education level, past diagnosis of depression, past diagnosis of psychotic disorder, whether they sought help during the intervention, baseline self-help for depression self-efficacy, and whether they had experienced an adverse life event in the six months prior to the development of sub-threshold depression.

Other outcomes include coping strategies used, knowledge of depression, and self-help for depression self-efficacy. In order to determine whether any change in depression might be due to changes in coping behaviour, the coping strategies used by participants will be evaluated. Usage rates and change in usage of each strategy in each intervention group will be compared pre- and post-intervention. Change in use of each strategy will be evaluated using logistic regression expressed as odds ratios with their 95% confidence intervals. Each strategy's mean perceived helpfulness for participants using them will also be compared pre- and post-intervention between groups.

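### The only pre-treatment PHQ-9 is the eligibility screen, yet the analysis takes change, onset and remission from a later baseline at which the PHQ-9 is not scheduled

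*Protocol article*

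**What the plan says.** On the outcome, the Assessment section states: "The primary outcome is depression symptom severity (assessed with the PHQ-9 [42"]). The same section fixes the first occasion: "Assessment is conducted at baseline (immediately prior to receiving the first Mood Memos email"). It points to Table 2 for the "outcome measures and time points of assessment". In that table the PHQ-9 row is marked at screening, mid-intervention, post-intervention and six months, and is blank at baseline. The K10 and WSAS rows are blank at screening and marked at baseline.

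The Trial procedure section gives the order of events. The PHQ-9 screen comes first, then: "Participants with a positive screen for sub-threshold depression will be assessed to see whether they meet further inclusion criteria". After that, "An email will be sent to the address provided, which will contain a link to the baseline questionnaire package". Finally, "Once the baseline assessment is completed, participants will be randomised to the active group or control group", and the first email follows at once. The section names no maximum time between the screen and the baseline package, and no second PHQ-9.

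The Statistical analysis section covers PHQ-9, K10 and WSAS scores in one mixed model for repeated measures (MMRM) plan, whose a priori "contrasts will compare change from baseline at the primary endpoint (post-intervention) and at 6-months follow up". Among the dichotomous outcomes, new major depression is counted "in participants who did not meet this criterion at baseline", and remission is counted in those who were sub-threshold at that same point.

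**The concern.** The schedule and the analysis use the word baseline for different occasions. For the two secondary scales it is the questionnaire package completed just before randomisation. For the primary outcome it can only be the earlier screen, and the article never says so.

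Two things follow. First, the screen score is the value on which people were selected, so it carries selection error: part of any later movement is regression to the mean. Second, depression status at randomisation is not observed. Someone who passed the five-symptom line, or recovered, after screening but before randomisation will be recorded as an onset or a remission during the trial. Prevention of major depression is part of the primary hypothesis in the Abstract, and a number needed to treat is promised for both events, so the definition of the at-risk group matters. No analysis plan can repair this afterwards, because a score not collected before randomisation cannot be recovered.

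**Working it through.** **1. The plan's own figure.** Inputs from Sample size: 0.2 SD, correlation 0.5, 80% power. Two-sided alpha of 0.05 and equal allocation are assumed.
- SD of change = √(2(1 − 0.5)) = 1.
- n = 2 × (1.960 + 0.842)² × 1² / 0.2² = 392.4, so 393 per arm, as stated.
- Dropout: 786 / (1 − 0.33) = 1174, close to the planned 1200.

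No stated number is wrong.

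**2. Is the blank cell an extraction fault?** In Table 2 the K10 and WSAS rows begin one column later than the PHQ-9 row. A column shift would have moved them together, so the blank is a scheduled choice.

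**3. What can baseline mean for the dichotomous outcomes?**
- If it means the screen: Trial procedure admits only sub-threshold screens, so the restrictions on who can have an onset or a remission exclude nobody.
- If it means the assessment just before the first email: the restrictions have content, but Table 2 collects no PHQ-9 with which to apply them.

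**4. How far does selection restrict the screen score?** Entry requires 2 to 4 symptoms. An item counts at a rating of 2 or 3, and suicidality counts from 1.
- Lowest total: suicidality at 1 plus one item at 2 = 3.
- Highest total: four counted items at 3, suicidality among them, plus five items at 1 = 12 + 5 = 17, on a scale of 0 to 27.

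**5. Regression to the mean (illustration).** Assume normal scores, an unselected correlation of 0.5, no treatment effect, and selection to a band from 0 to 1.5 SD on the screen.
- Mean selected score = (0.3989 − 0.1295) / 0.4332 = 0.62 SD.
- Expected change = (0.5 − 1) × 0.62 = −0.31 SD.

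A simulation on these assumptions gave −0.31 SD in each arm. Within-arm improvement is overstated, and the difference between arms is zero, as it should be.

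**6. Dilution of the relative risk (illustration, all inputs assumed).** Let a share s of control-arm onsets predate randomisation, with equal numbers in each arm that the emails do not alter. The observed relative risk is s + (1 − s) × true relative risk. For a true value of 0.70:
- s = 0.10: 0.10 + 0.90 × 0.70 = 0.73.
- s = 0.30: 0.30 + 0.70 × 0.70 = 0.79.

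The real s is unknown, because status at randomisation is not measured.

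**7. Does selection erode power?** Take unselected SDs of 1 and r = 0.5, and let selection cut the SD of the screen score to a fraction k.
- k = 0.6: post-score variance = 0.25 × 0.36 + 0.75 = 0.84, SD 0.917; r = 0.5 × 0.6 / 0.917 = 0.33.
- k = 0.8: variance = 0.25 × 0.64 + 0.75 = 0.91, SD 0.954; r = 0.5 × 0.8 / 0.954 = 0.42.
- Residual SD given the screen score, in both cases: √0.75 = 0.866, the same as without selection.

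The correlation falls, but the residual SD does not change. Baseline-adjusted power at 393 per arm for 0.2 unselected SD therefore stays at about 90%.

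**The case against.** The strongest reply is that this is a labelling matter. Every randomised participant completes the PHQ-9 before randomisation, so a pre-treatment value exists for all and can serve as baseline. Regression to the mean and drift fall equally on both arms, so the primary comparison is sound. All of that stands. A reader might infer from Table 2 that the primary outcome has no baseline measurement at all, and that would be wrong. What is missing is a PHQ-9 at the baseline assessment and a statement that the screen takes its place.

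A reader might also infer that the screen score can be of any age. The document does not support this either. It states no limit, but it is a condensed article, and a link expiry may be set in the full protocol.

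A third tempting inference is that range restriction leaves the trial underpowered. It does not follow: with the effect held on the unselected scale, the residual SD is unchanged. If the 0.2 SD and the correlation of 0.5 were already meant for the selected population, no restriction correction applies.

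Two further points have some force. Dilution of the relative risk requires the emails to act less on people who had already worsened by randomisation, which the article does not address, so it is possible rather than shown. And because the PHQ-9 looks back two weeks, a prompt repeat would largely cover the same period, in a study that keeps its questionnaires short to limit dropout. A repeat is still a reading on which nobody was selected, and it is the only way to observe status at randomisation.

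**Conclusion.** The point holds in a limited form. The PHQ-9 schedule in Table 2 does not match the definition of baseline in Assessment or the use of baseline in Statistical analysis, and the three must be reconciled. The randomised contrast is unbiased, and the sample size of 393 per arm is not contradicted.

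The consequences are inflated within-arm change and inflated onset and remission rates, with the numbers needed to treat resting on the same counts; a relative risk for onset that may be pulled towards 1; and the precision forgone by not having a second, unselected pre-treatment score in the model. None of these can be sized from the document. The −0.31 SD and the 0.73 to 0.79 range are illustrations under stated assumptions, not estimates for this trial. It is worth changing before recruitment because it concerns data collection and cannot be put right later.

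**What to change.** **Preferred.** Add the PHQ-9 and its impact item to the baseline package and mark the cell in Table 2.
- Keep the screen for eligibility only.
- In the MMRM, use the baseline score, with the screen score as a second covariate.
- Define the groups at risk of onset and eligible for remission by status at baseline.
- Keep all randomised participants in the severity analysis.

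**Minimum, if the PHQ-9 is not repeated.** State that the screening PHQ-9 is the baseline value. Set a maximum interval from screening to randomisation and report its distribution. Reword the change, onset and remission definitions in Statistical analysis so that they refer to the screen.

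**Cost.** About ten items, assumed to take about one minute, in a package estimated at 6 minutes. Any extra dropout falls before randomisation, so it does not affect the comparison. The team would also have to state how a participant whose status has changed by the baseline reading is handled. That is a trial management decision outside this point. The minimum version costs only wording, plus an interval limit in the automated system if none exists already.

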### Depression

The depression module of the Patient Health Questionnaire (PHQ-9) [45] will be used to assess depression. It is a self-rated questionnaire that makes probable diagnoses of mental disorders based on DSM-IV criteria [46]. The PHQ-9 consists of items covering the 9 symptoms of criterion A for a DSM-IV diagnosis of Major Depressive Episode [16]. Each item is rated in terms of its frequency over the last two weeks, from 0 (not at all) to 3 (nearly every day). Its structure means it can be used both to make probable diagnoses of major depression and sub-threshold depression, as well as to measure the severity of symptoms (0 to 27). An additional question asks about the impact of the symptoms on the person's functioning, analogous to criterion C of DSM-IV Major Depressive Episode [16]. The PHQ-9 has excellent reliability assessed by internal-consistency [45,47,48], adequate test-retest reliability [45,49], excellent criterion validity [50], and is sensitive to change [47,51]. It has been used in studies of internet treatment of depression [52], to assess rates of sub-threshold depression in the community [53], and to measure treatment of sub-threshold depression in primary care [54].

### Psychological distress

The K10 [43,55] will assess non-specific psychological distress. The K10 measures 10 symptoms of mental health in the anxiety-depression spectrum, using a 5-point response scale based on the amount of time the respondent has experienced the symptom in the past 30 days. Using the Australian scoring method [56] scores range from 10 (no distress) to 50 (severe distress). It is widely used as a screening tool in population surveys [56,57] and as an outcome measure in mental health services [58], as well as in some depression treatment studies [52,59]. It has good internal consistency [55,60] and is a good discriminator of community cases and non-cases of DSM-IV disorders [61]. It also has good reliability and validity when completed on the internet [60].

### Functioning

Functioning will be assessed with the Work and Social Adjustment Scale (WSAS) [44]. This is a brief, 5-item scale that measures impairment attributable to an identified problem in work, home management, social activities, private leisure activities, and ability to form and maintain relationships. Scores range from 0 to 40, with a score above 20 suggesting moderate to severe psychopathology, scores between 10 and 20 suggesting significant functional impairment but less severe symptomatology, and scores below 10 being associated with subclinical populations. The scale has strong psychometric properties, with good internal consistency, test-retest reliability, alternate forms reliability, and good convergence with scores on the Hamilton Rating Scale for Depression and patient ratings of perceived improvement [44]. It has also been used in online studies of depression treatment [62,63].

Several other assessment tools will be used in addition to those described above.

### List of Threatening Experiences

The List of Threatening Experiences (LTE) is a brief measure of the occurrence of negative life events in the past six months. It records common events that are likely to be threatening and of aetiological importance to psychiatric disorders [64,65]. Twelve events (e.g., you broke off a steady relationship) are scored as being present or absent in the past six months. This measure was included at baseline as a potential predictor of intervention response, as it could be argued that the self-help strategies endorsed in the Mood Memos would not be helpful for those whose depression symptoms were due to significant life events. A reliability study showed the LTE has adequate test-retest reliability, agreement ratings with other informants on the events were good, and it has good concurrent validity [65]. The scale has been used in several large population surveys (e.g. [66,67]).

### Coping questionnaire

Participants are asked to rate the frequency and perceived helpfulness of 26 coping strategies for depression symptoms over the past month at baseline and at post intervention. The coping strategies include the 14 used in the Mood Memos emails, as well as other strategies that were rated in the expert study [10] as relatively unhelpful (e.g., *you drank alcohol*) or unlikely to be helpful (e.g., *you had a warm bath*). These were assessed to determine participants' coping repertoire at baseline, whether the intervention changed their coping strategies, and whether this was related to intervention response. Frequency of use is rated on a 5-category scale (*not at all*, *infrequently*, *moderately frequently*, *very frequently*, *don't know*), and perceived helpfulness on a 5-category scale (*not at all helpful*, *a little helpful*, *moderately helpful*, *very helpful*, *don't know*). Participants are asked to rate a strategy's perceived helpfulness only if they have indicated they had used the strategy (*infrequently *to *very frequently*) in the past month.

